#### Step 2: Semistructured Interviews—Recruitment and Information-Gathering Procedures

The research team will invite all intervention FMG and home care professionals involved in the GPS intervention (pharmacists, nurses, and physicians) to an individual telephone interview at the end of the implementation period (ie, 18 months after inclusion of the first older adults). We will obtain verbal consent from the health care professionals before conducting the interview, which will last 30 to 45 minutes. We will aim for a total of approximately 30 interviews—that is, at least 1 pharmacist, 2 FMG nurses, and 2 physicians per FMG (n=25) and 6 nurses or nursing assistants from the home care team. This number should be sufficient to gather all the various health care professionals’ experiences while being feasible in the context of FMGs. A qualified interviewer will conduct the interviews using a semistructured interview guide to explore their views on the intervention. The interview will cover categories proposed by Patton’s Theoretical Model of Change [34]: (1) resources required for support, training, and coaching; (2) activities required by the model; (3) participation in the model’s implementation; (4) reactions to and satisfaction with the model; (5) changes in knowledge, attitudes, and skills; (6) change in practice; and (7) perceived results of the model. We will also invite professionals to complete the pretested French version of the web-based NoMAD instrument [35,36] derived from the Normalization Process Theory [37] after the end of the implementation period.

### Data Analysis

In step 1, we will use an intention-to-treat approach to assess the GPS intervention’s effectiveness. The principal analysis will compare the difference (1) in the average number of medications per person between the unexposed and exposed groups according to the study period (baseline and 6 months) and (2) the average number of potentially inappropriate medications per person between the 2 groups, according to the study period, by mixed Poisson repeated measures regression. This type of analysis considers intra-FMG and intraindividual correlations. Contrasts will be built to determine if the average number of medications per person over time differs between the exposed and the unexposed group. Secondary results will be analyzed similarly to compare the MTBQ, PESQ, and EQ-5D-5L scores between the groups exposed and unexposed to the GPS intervention.

Medication data missing at measurement time periods after the initial data collection will be imputed using the last-observation-carried-forward method. Using this method, the potential benefits of the intervention should be underestimated. For participants lost to follow-up regarding the questionnaires, no measures will be imputed at follow-up, but sensitivity analyses may be used in which baseline questionnaires scores could be imputed for follow-up scores. We will perform all analyses with SAS statistical software (SAS Institute Inc).

In step 2, we will record the interviews and transcribe them verbatim to then perform qualitative thematic content analysis. The first stage of this analysis consists of coding the data using NVivo qualitative analysis software (QSR International). We will develop a codebook based on Patton’s Theoretical Model of Change [34] for this purpose. Two research agents will independently test the first version of the codebook by coding excerpts of a few interviews. They will discuss and improve this version and test it again by coding excerpts of other interviews. This procedure aims to obtain a rigorous coding of the interviews and an accurate description of the experiences. The final sequential analysis will allow the integration of the quantitative results on the intervention’s impacts with the qualitative results describing the experiences of the FMG and home care teams. We will build and present an integration matrix and discuss it with the members of the research team and the stakeholders with whom the project was initiated, as well as with patient partners. This process will identify crucial elements for improving the intervention for future implementation.

According to mixed methods research methodology, the quantitative results obtained at step 1 will be interpreted and discussed in the light of information obtained from step 2, so that lessons can be learned on how to best implement such an interdisciplinary practice change, including the increased roles of some of the players [38].

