## Methods

### Study Design

We based our methodology on the Medical Research Council's conceptual model on how to evaluate complex interventions [25]. We will use mixed methods, including a quasi-experimental controlled trial (step 1) and semistructured interviews (step 2). For step 1, information on health conditions and medication utilization at study entry and follow-up (ie, after 6 months) will be collected for all included participants. Participating patients will also complete 3 validated questionnaires in either French or English to assess their perceived treatment burden, quality of life, and satisfaction with care. The Multimorbidity Treatment Burden Questionnaire, (MTBQ) [26,27], the EQ-5D-5L [28], and the self-administered Physician Enabling Skill Questionnaire (PESQ) [29] will be used. Pharmacists will also report their interventions and suggestions during the 6-month follow-up. In step 2, we will invite all health professionals who implemented the intervention (ie, pharmacists, nurses, and physicians) to participate in a semistructured interview where they will be asked about the ease to integrate the intervention into their practice, their satisfaction with it, and their perception of its impacts for older adults and their families.

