### Study Setting

The study will comprise participants from an exposed group of approximately 5 FMGs with attending pharmacists who will implement the intervention and a control group composed of participants from 5 others FMGs without involved pharmacists. FMGs and home care teams will participate at their convenience within 2 Integrated (University) Health and Social Services Centers territories: (1) the *Centre intégré universitaire de santé et de services sociaux* (CIUSSS) *du Nord-de-l’Ile-de-Montréal* (NIM) in a metropolitan area and (2) the *Centre intégré de santé et de services sociaux* (CISSS) *de Chaudière-Appalaches* (CA) in a mixed—urban and rural—area. We used this selection process to facilitate implementation as the intervention teams need to be motivated toward its application and training and mentoring activities. To be eligible for participation, intervention FMGs must have at least 1 participating pharmacist, interested partner nurses, and physicians. Similarly, intervention home care teams must have access to a participating FMG pharmacist and a home care nurse. In contrast, in control FMGs and their home care teams, no FMG pharmacist will be systematically involved in the eligible patients’ trajectory. However, the FMGs must be willing to allow data collection and delay implementing similar interventions within their teams.

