### Study Population

For the first step, the intervention targets 2 patient subgroups at turning points: (1) older adults undergoing cognitive evaluation or recently diagnosed with MNCDs in FMGs and (2) older adults with MNCDs followed at home by the home care teams.

For the second step, FMG professionals and home care teams implementing the intervention are also targeted.

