#### Step 1: Quasi-experimental Controlled Trial

##### Inclusion and Exclusion Criteria for Older Adults

All older adults (aged ≥65 years) undergoing cognitive evaluation at the FMG OR referred to a memory clinic OR having been diagnosed with MNCDs at the FMG within the last year OR followed up at home for a MNCD AND referred to the pharmacist in the intervention FMGs will be invited. We will exclude older adults in palliative care or those who do not understand French or English (without a caregiver who could assist them).

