##### Sampling Method, Recruitment, and Data Collection Procedure

We will conduct a quasi-experimental (ie, rather than a randomized) study given that our intervention will depend on whether an older adult’s FMG includes a participating pharmacist (intervention group) or not (control group).

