## Results

All study materials (questionnaires, patients’ recruitment tools, and training documents) have been developed in collaboration with clinicians and patient partners. As of September 2022, 13 FMGs have agreed to participate in the GPS project (11 implementing the intervention and 2 as controls). We have yet to recruit more FMGs that will be part of the control group. Recruitment of older adults began in September 2021, when the project was launched. We had planned 12 months for the inclusion of eligible older adults. As of September 2022, a total of 100 participants had been enrolled and the follow-up was completed for 23 of them. Data collection will take approximately 18 months, and data analysis and synthesis of the results will take another 9 months. Knowledge transfer/mentoring sessions will be organized regularly during the implementation period (ten 1-hour meetings in each CI[U]SSS have been realized as of September 2022) and are also planned after the end of the GPS study (approximatively 6 months). These sessions are open to FMG pharmacists, physicians, mentors (physicians and pharmacists with geriatric expertise), and research team members and comprise short presentations of specific clinical interest, summaries of issues surrounding the study methods and procedures, as well as an occasion for an exchange between all these persons on clinical and research questions.

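### The stated primary contrast of this non-randomised trial names no control for confounding, so any difference in six-month medication trend between arms would be credited to the GPS intervention

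*Protocol article*

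**What the plan says.** **Design.** Exposure follows the FMG, according to its having a participating pharmacist or not, and the article gives this as the reason for not randomising: "We will conduct a quasi-experimental (ie, rather than a randomized) study given that our intervention will depend on whether" (sentence cut here; it stands under Sampling Method, Recruitment, and Data Collection Procedure).

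**Selection of FMGs.** Study Setting states that "FMGs and home care teams will participate at their convenience", and explains: "We used this selection process to facilitate implementation as the intervention teams need to be motivated toward its application". Sites lie in two unlike regions, one metropolitan and one mixed urban and rural.

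**Patients.** Two subgroups are pooled: people under cognitive evaluation or recently diagnosed in the FMG, and "older adults with MNCDs followed at home by the home care teams". In intervention FMGs, patients who meet a clinical criterion "AND referred to the pharmacist in the intervention FMGs will be invited". In control FMGs there is no referral; eligible patients are found from records and by asking staff (Sample Size Calculation).

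**Inclusion date.** It is the referral date in the intervention arm and the identification date in the control arm. For home care patients one rule is given, the first home visit after study start.

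**Timing.** Results reports recruitment from September 2021, with 12 months planned for inclusion. In September 2022 there were 11 intervention and 2 control FMGs, and "We have yet to recruit more FMGs that will be part of the control group".

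**Analysis.** Data Analysis compares groups by study period with mixed Poisson repeated-measures regression: "Contrasts will be built to determine if the average number of medications per person over time differs between the exposed and the unexposed group". The model is credited with handling correlation within FMGs and within individuals. No covariate, matching, weighting, region term or calendar term is mentioned.

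**The concern.** In a randomised trial, adjustment mainly buys precision. Here the effectiveness claim depends on how the arms are made comparable, and the stated model addresses only correlation. Random effects for FMG and patient correct the standard error; they do not make the groups' expected trends equal.

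Comparing changes rather than levels helps: a stable difference between FMGs or patients largely cancels (on the log scale, given a Poisson model). What does not cancel is a difference in how medication counts would have moved over six months without GPS. Someone whom a clinician has just referred and someone found by a record search need not be at the same point in their care. Nor need a person newly assessed for cognition and a person already followed at home. If such features are unevenly spread between arms, the contrast mixes their trend with the effect of the pharmacist, and the reader cannot separate the two.

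**Working it through.** **1. What the contrast estimates.** Let patient *i* have a time-constant covariate *x* (for example home care = 1, FMG subgroup = 0). Write the change from baseline to 6 months, on the model's scale, as

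change = common trend + *d* × group + *h* × *x*,

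where *d* is the GPS effect and *h* the difference in trend between subgroups. Without *x* in the change, the expected group contrast is

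*d* + *h* × (share of *x* in intervention arm − share of *x* in control arm).

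The second term is the bias. It is zero if the shares are equal or if *h* = 0, which is the parallel-trends condition.

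**2. Why main effects do not help.** A main effect of *x* adds the same amount at baseline and at 6 months, so it drops out of the change. Data Analysis fills missing follow-up medication counts by last observation carried forward, so patients with a baseline contribute both periods and the cancellation is close to complete. Only an *x*-by-time term reaches *h*.

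**3. Illustrative size.** The article gives no shares by arm and no trends. Assume home care is 50% of one arm and 20% of the other, a 30-point imbalance:

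| Assumed subgroup drift over 6 months | Bias = 0.30 × drift | Share of the 1-medication target |
|---|---|---|
| 0.25 | 0.075 | about 8% |
| 0.5 | 0.15 | 15% |
| 1.0 | 0.30 | 30% |

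**4. The plan's own figure.** Sample Size Calculation claims 83% power for a difference of 1 medication, with 5 + 5 FMGs, 40 patients each and an intracluster correlation of 0.005. No standard deviation, alpha or sidedness is given, so the figure can only be solved backwards:

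- design effect = 1 + (40 − 1) × 0.005 = 1.195
- effective n per arm = 200 / 1.195 = 167.4
- at two-sided 5% with a normal approximation, 83% power implies an SD of change of 3.14
- standard error of the contrast = 3.14 × √(2 / 167.4) = 0.343

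Other conventions imply SD 3.52 (one-sided 5%) or 2.75 (two-sided *t* with 8 df). The 83% is neither confirmed nor refuted.

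**5. Effect on error rate.** With no GPS effect and a trend difference *b*, the chance of a nominally significant result is Φ(−1.96 − *b*/0.343) + 1 − Φ(1.96 − *b*/0.343):

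| *b* (medications) | False-positive rate |
|---|---|
| 0 | 5% |
| 0.1 | 6% |
| 0.3 | 14% |
| 0.5 | 31% |

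These rates rest on the back-solved SD and on assumed values of *b*, on the additive scale on which the target is expressed.

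**The case against.** **The article is condensed.** It names a model class, the correlations and the contrast; it does not rule out covariates, and a list may stand in a full protocol or analysis plan that is not shown. This stands in part: a reader might infer that the analysis is definitely unadjusted, and silence does not prove that. But what is described is a group-by-period contrast. The only line on adjustment, in the Discussion, follows remarks on participants' understanding and data collection, is conditional and names no method, so it does not settle the matter.

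**No difference in patient mix is shown.** A reader might infer that the arms do differ in mix and that the estimate is biased. The article has no baseline figures by arm, and home care teams are planned in both arms. The entry routes make a difference plausible, not established, and nothing in the article documents unequal trends between subgroups or regions.

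**Calendar time.** A reader might infer that controls are simply recruited later. By September 2022 two control FMGs had agreed and 100 participants were enrolled, against a planned 10 × 40 = 400. If that target is kept, most enrolment in both arms lies ahead and overlap may be substantial. Later recruitment of controls is probable, but its extent is unknown.

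**Comparing changes already does much of the work.** True for stable differences. It leaves trends, which is the whole of this point.

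**Conclusion.** The point holds as a weakness in the stated method, not as a demonstrated bias. Followed as written, the primary contrast assigns any difference in six-month trend to GPS, in a design where selection of FMGs, entry route and inclusion date differ by arm and recruitment timing probably does too. The documents do not show that such a difference exists, nor in which direction it would run. The range of 0.08 to 0.30 medication depends entirely on the assumed 30-point imbalance and the assumed drift of 0.25 to 1 medication; the upper end takes a drift as large as the target effect itself. The control of confounding should be fixed before outcomes are compared, since covariates chosen afterwards would carry much less weight.

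**What to change.** - **Primary analysis.** Make the group-by-time contrast adjusted, with pre-specified covariate-by-time terms for patient subgroup (FMG evaluation or recent diagnosis versus home care), region, age and number of health conditions. Study Design says that "information on health conditions and medication utilization at study entry and follow-up (ie, after 6 months) will be collected for all included participants"; subgroup and region follow from how and where the patient enters, and age is needed for eligibility.
- **Supporting analyses.** Report the unadjusted contrast as secondary, add an overlap-weighted sensitivity analysis, and state the parallel-trends assumption.
- **Calendar period.** Examine it in a sensitivity analysis restricted to the window in which both arms enrol. It may be nearly collinear with arm, so a period-by-time term in the primary model could fail to separate the two.
- **What not to do.** Control inclusion dates should not be moved back to match the intervention arm. That would be a design change: it conflicts with the identification-date rule, separates the medication baseline from the questionnaire baseline, and places inclusion before consent.

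The cost is analysis-plan wording, modest programming and some loss of precision, mainly from region, which is an FMG-level variable with few control FMGs. None of these covariates measures team motivation, so residual confounding from that source remains and should be acknowledged as a limitation.

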##### Outcomes Measures

The primary outcome measure is the change in the number of prescribed medications. Specifically, (1) the total number of prescribed medications and (2) the number of potentially inappropriate medications according to the Beers criteria [33] will be measured in the intervention and control groups. We will obtain data from patients’ medical records at the beginning (baseline) and 6 months after inclusion in the study.

We will assess several secondary outcome measures. First, a change in the treatment burden level will be measured with the 13-item MTBQ [26,27] in the intervention and control groups at baseline and 6 months follow-up. We will score each item as follows: 0 (not difficult/does not apply), 1 (a little difficult), 2 (quite difficult), 3 (very difficult), and 4 (extremely difficult). We will interpret the scores as suggested by the authors of the original MTBQ instrument: no burden (score 0), low burden (score <10), medium burden (score 10-22), and high burden (score ≥22) [26].

Second, we will measure the quality of life in the intervention and control groups at baseline and 6 months follow-up with the EQ-5D-5L [28]. The descriptive system comprises 5 dimensions: mobility, self-care, usual activities, pain/discomfort, and anxiety/depression. Each dimension has 5 levels: no problems, slight problems, moderate problems, severe problems, and extreme problems. Responses are coded as single-digit numbers expressing the severity level selected in each dimension [28]. The last study outcome is the satisfaction with the care received and access to care. To measure this outcome, the PESQ, validated in Quebec primary care settings, will be used [29]. We have adapted the questions with the author’s approval to consider not only the physician but the whole FMG team.

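### The only model named is a Poisson mixed model, and the MTBQ, PESQ and EQ-5D-5L scores are to be analysed likewise; on the plain reading, a count model is fitted to scores that are not counts

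*Protocol article*

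**What the plan says.** In the protocol article, Data Analysis, the two medication outcomes are compared between groups "according to the study period, by mixed Poisson repeated measures regression". The next sentence gives the reason for the choice: "This type of analysis considers intra-FMG and intraindividual correlations". After a sentence on contrasts comes the rule for everything else: "Secondary results will be analyzed similarly to compare the MTBQ, PESQ, and EQ-5D-5L scores between the groups exposed and unexposed to the GPS intervention". No other distribution, link, dispersion parameter or robust variance is named.

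Outcomes Measures describes the three instruments:

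- **MTBQ.** 13 items: "We will score each item as follows: 0 (not difficult/does not apply), 1 (a little difficult", and so on up to 4. How the items are combined is not stated. The bands are "no burden (score 0), low burden (score <10), medium burden (score 10-22), and high burden (score ≥22".
- **EQ-5D-5L.** Five dimensions with five levels each: "Responses are coded as single-digit numbers expressing the severity level selected in each dimension". No index or sum is defined.
- **PESQ.** "To measure this outcome, the PESQ, validated in Quebec primary care settings, will be used". Its scoring is not described.

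These instruments carry hypotheses 3 to 5 of the five listed at the end of the Introduction: burden, satisfaction and quality of life.

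**The concern.** A Poisson model ties the variance to the mean. That is a sensible start for a number of medications. It has no basis for a bounded rating-scale score, whose spread is set by the instrument and by how the items are combined. Two things follow when the standard error is taken from the model:

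- The estimated ratio between groups does not change when a score is rescaled, but its standard error does. Significance then depends on an arbitrary choice of unit, and the article leaves that unit open.
- Depending on the score's mean, SD and within-person correlation, the standard error may be too small (false claims of reduced burden) or far too large (real gains in satisfaction or quality of life missed).

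A related gap is that the analysis compares EQ-5D-5L scores, while the outcome section defines only five separate codes, so there is no single score to enter into any regression.

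**Working it through.** **The plan's own figures.** None exists for the secondary scores. The one statistical figure, 83% power for a difference of 1 medication, concerns the primary outcome and is not an input here. It cannot be reproduced because neither SD nor alpha is given. With a design effect of 1 + 39 × 0.005 = 1.195 and 200/1.195 = 167.4 effective patients per group, it implies an SD of change of about 3.14 (two-sided 5%, normal approximation).

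**Inputs from the article.** 5 + 5 FMGs with 40 patients each, so 200 per group; two time points; MTBQ 13 items scored 0–4, so a plain sum runs from 0 to 13 × 4 = 52.

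**Assumptions.** All means, SDs and correlations below, and the index, mean-score and 0–100 scales. The article gives none of these.

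**1. Dependence on the unit.** Multiply a score by c. Means are multiplied by c, so the log ratio is unchanged. The Poisson variance of a log mean is proportional to 1/mean, so the model-based SE is divided by √c and z is multiplied by √c. For the MTBQ on 0–100 instead of 0–52, √(100/52) = 1.39. As an example, z = 1.50 (p = 0.13) becomes 1.50 × 1.387 = 2.08 (p = 0.04) on the same data. This step needs no mean or SD, but it does need a Poisson model with model-based SEs.

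**2. Size of the error.** For the group-by-time log ratio with a patient random intercept, the true variance is proportional to SD²(1 − ρ) and the model's variance to the mean. Hence

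true SE / model SE = k = √[SD²(1 − ρ)/mean], and type I error = 2[1 − Φ(1.96/k)].

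For the MTBQ sum at ρ = 0.6: 7.8² × 0.4/7.8 = 3.12, k = 1.77, type I error 0.27.

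| Score (assumed mean, SD) | k for ρ = 0.4 down to k for ρ = 0.8 | Type I error |
|---|---|---|
| MTBQ sum 0–52 (7.8, 7.8) | 2.16 to 1.25 | 0.36 to 0.12 |
| MTBQ 0–100 (15, 15) | 3.00 to 1.73 | 0.51 to 0.26 |
| EQ index 0–1 (0.7, 0.2) | 0.19 to 0.11 | about 0 |
| EQ index × 100 (70, 20) | 1.85 to 1.07 | 0.29 to 0.07 |
| EQ sum of codes 5–25 (10, 3.5) | 0.86 to 0.49 | 0.02 to 0.0001 |
| PESQ mean 1–5 (4, 0.7) | 0.27 to 0.16 | about 0 |
| PESQ 0–100 (75, 17.5) | 1.57 to 0.90 | 0.21 to 0.03 |

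**3. Power where the SE is too large.** Take a 0.3 SD effect, ρ = 0.6, 200 per group. The correct SE in SD units is √(4 × 0.4/200) = 0.0894, so z = 0.3/0.0894 = 3.35 and power is Φ(3.35 − 1.96) = 0.92. For the 0–1 index, the Poisson SE on the score scale is √(4 × 0.7/200) = 0.118, so the effect of 0.06 would have to exceed 1.96 × 0.118 = 0.23. Power is about 0. For the 1–5 mean score, an effect of 0.21 would have to exceed 1.96 × √(4 × 4/200) = 0.55. Power is again about 0.

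**4. Simulation with no effect.** 300 runs, 200 per group, two visits, Poisson mixed model with a patient random intercept, no FMG effect.

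| Score | Mean model SE | Type I, model SE | Type I, empirical SE |
|---|---|---|---|
| MTBQ 0–52 | 0.0504 | 0.233 | 0.047 |
| MTBQ 0–100 | 0.0363 | 0.363 | 0.030 |
| EQ index 0–1 | 0.1675 | 0.000 | 0.060 |
| EQ index × 100 | 0.0168 | 0.170 | 0.060 |
| PESQ mean 1–5 | 0.0709 | 0.000 | 0.050 |
| PESQ mean × 20 | 0.0159 | 0.033 | 0.060 |

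The model SE for the MTBQ falls by 0.0504/0.0363 = 1.39, as step 1 predicts. The patient random intercept does not cure the problem; an empirical variance does, on every scale tried.

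**5. MTBQ bands.** A score of 22 meets both "medium burden (score 10-22), and high burden (score ≥22". On a plain item sum 22 is attainable.

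**The case against.** The strongest reply is that the article never says outright that Poisson regression applies to the scores. The Poisson model is named in the sentence on medication counts. The sentences that follow concern correlation and contrasts, and *similarly* may refer only to that mixed repeated-measures structure, with a distribution suited to each score set out in the full plan. That reading is possible. It does not remove the point: this is a positive statement about the secondary analysis, not silence, and the only model it can refer back to is a Poisson one.

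A reader might go further and infer that the secondary standard errors and p-values are simply wrong. The article does not support that. The error arises only with model-based variance and no dispersion or robust correction, and the article specifies neither. The factor of 1.39 carries the same condition.

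Nor is the direction fixed for every score. With an equally assumed mean of 10, SD of 7 and ρ of 0.8, the within-person variance is 49 × 0.2 = 9.8 against a Poisson variance of 10, and the error all but disappears. The figures above are therefore ranges under assumptions, not predictions.

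It is also fair to say that the overlap at 22 touches no planned test. The bands serve interpretation and the analysis compares scores. Whether 22 can occur on the scale to which the cut-points apply depends on a scoring rule the article does not give.

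**Conclusion.** The point holds in a conditional form. As written, the only named model is a count model, and the plain reading carries it over to three instruments that are not counts. If that is done with model-based standard errors, inference for hypotheses 3 to 5 depends on the score unit. Under the assumed means and SDs and ρ of 0.4 to 0.8, type I error would be about 0.12 to 0.36 for an MTBQ sum, and about 0 for a 0–1 index or a 1–5 mean score. At ρ = 0.6, the latter two would have almost no power for a 0.3 SD effect that a correct SE would detect with about 92% power.

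The unit dependence does not rest on the assumed means and SDs; the size and direction of the error do. The primary medication counts are outside this point. Severity: should-fix, secondary outcomes only.

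**What to change.** Replace the sentence on secondary results with one that names the model: linear mixed models for the MTBQ, PESQ and EQ-5D-5L scores, with group, time and group-by-time terms and random effects for patient and FMG. Add an ordinal model or a bootstrap as a sensitivity analysis if the MTBQ is strongly skewed. If cluster-robust standard errors are used, state a small-sample correction, because only about 10 FMGs are planned.

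In Outcomes Measures, define the EQ-5D-5L summary score to be analysed in place of the five separate codes, and state how the MTBQ and PESQ totals are formed. As a minor point, make the MTBQ bands mutually exclusive at 22 and state the scale they apply to.

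The cost is a few sentences before analysis begins. Recruitment, data collection and the primary analysis do not change.
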